## Introduction

Spasticity is defined as a velocity-dependent increase in muscle stretch resistance [1], which is associated with increased muscle tone. Spasticity is one of the leading causes of impaired motor control and thus significant functional limitations in the upper limb, particularly in cases of Cerebral Palsy (CP), after traumatic brain injury, and following strokes. In the upper limb, the most common patterns include spasticity leading to shoulder adduction, shoulder internal rotation, elbow flexion, forearm pronation, wrist flexion and ulnar deviation, finger flexion, “thumb-in-palm” deformity, clenched fist, and swan-neck deformities of the fingers due to hyperactivity of the intrinsic muscles. If left untreated, spasticity can lead to muscle and later joint contractures, resulting in progressive functional loss of the upper limb and care problems.

The standardized clinical examination of patients with upper limb spasticity includes the assessment of muscle strength grades (MRC scale), as well as the assessment of muscle tone and the extent of spasticity using clinical scales (modified Ashworth Scale (MAS) [2] and Tardieu Scale (TS) [3]), and functional tests including video recordings (Leclercq 2003).

Conservative treatment methods include physiotherapy, occupational therapy, and splint therapy, possibly combined with oral antispastic medication or intrathecal administration of Baclofen®. After exhausting conservative therapy options, and depending on the level of suffering and the patient’s wishes, surgical therapy can be performed. This usually consists of a combination of tendon and nerve procedures. By means of intramuscular lengthening (fractional lengthening), release of the muscle aponeurosis, tendon lengthening (Z-lengthening), or possibly tenotomies, the overactivity of the spastic muscles is reduced, and optimally, the full range of motion of the adjacent joints is restored [4,5]. If this is not successful, additional arthrolysis or even arthrodesis may need to be considered. An essential second pillar of surgical therapy are the so-called hyperselective neurotomies (HSN), which are less commonly studied. In HSN, 2/3 of the nerve fibers innervating a particular muscle are severed to reduce or eliminate the spasticity of that muscle without loss of strength [6–8].

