## Hypotheses

The combination of 3D motion analysis and sEMG is suitable for objectively detecting spasticity in wrist and finger flexors, providing an effective preoperative assessment tool for surgical therapy strategy and postoperative outcome control.

To test the central hypothesis, the following sub-hypotheses will be investigated

a)Simultaneous recording of sEMG signals from all wrist flexors, extensors, and extrinsic finger extensors and flexors, as well as capturing all joint angles distal to the forearm using 3D motion analysis, is feasible in healthy participants and patients with spasticity.b)The combination of 3D motion analysis and sEMG measurement allows for a reliable measurement of wrist and finger spasticity.c)Objective detection of wrist and finger spasticity can be performed within a clinically acceptable timeframe.d)The proposed methodology is suitable for measuring postoperative improvement of wrist and finger spasticity after hyperselective neurectomy, tendon lengthening, and/ or transposition.e)A musculoskeletal modeling generated from 3D motion analysis can predict the postoperative outcome after surgical treatment for upper limb spasticity based on preoperative measurements.

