**Inclusion criteria:**
No previous injuries of the upper extremityNo neurological impairmentsInformed consent**Patients**: Patients with upper limb spasticity will be recruited during consultations in a specialized outpatient clinic when presenting for evaluation regarding potential surgical intervention. Clinical assessments in the movement laboratory will be conducted preoperatively (and potentially a second time one week later), 6 months postoperatively, and 1 year postoperatively if surgery is performed. The approximate duration of each measurement is one hour.**Inclusion criteria**:Patients with spasticity of the upper extremity and an indication for surgery

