### Sample size calculation

Based on our preliminary work, the following effect size and resulting sample size were calculated for the primary outcome parameter, EMGchange, during passive stretch of the biceps brachii in patients with elbow flexor spasticity (one-sided, α = 0.05, power (1–β) = 0.8) compared to healthy participants. (Table 1)

**Table 1 pone.0328528.t001:** Sample size calculation based on the primary outcome parameter (EMGchange (%MVIC)); SD = standard deviation.

Parameter	Mean (patient)	SD (patient)	Mean (healthy)	SD (healthy)	Effect Size	Sample Size per group
EMGchange	19.1	21.1	0.04	0.1	0.91	10

The sample size calculation for the pre-/post-surgical comparison is based on our preliminary data. In a group of 7 patients with elbow flexor spasticity who underwent hyperselective neurectomy (HSN) of the elbow flexors as a surgical treatment, we were able to perform objective spasticity testing of the elbow. For the primary outcome parameter, EMGchange, the following effect size and resulting sample size were determined (one-sided, α = 0.05, power (1-β) = 0.8) (Table 2):

**Table 2 pone.0328528.t002:** Sample size calculation for a pre-/post-analysis based on the primary outcome parameter (EMGchange (%MVIC)) in 7 patients with elbow flexor spasticity who underwent hyperselective neurectomy (HSN) of the elbow flexors; SD = standard deviation.

Parameter	Mean preop	SD preop	Mean postop	SD postop	Effect Size	Sample Size
EMGchange (n = 7)	21.7	23.7	7.4	4.2	0.65	16

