After analyzing the preoperative and 6 months postoperative measurements from a minimum of 15 patients, a first interim analysis will be conducted using a paired two-sample t-test to determine any significant changes in the defined outcome parameters (EMG LV, EMG HV, EMGchange, extension deficit for wrist flexors (FCR, FCU), and finger flexors (FPL, FDP, and FDS)). If normal distribution is not confirmed, the Wilcoxon test will be applied.

Upon completion of all postoperative measurements, changes in the defined outcome parameters (EMG LV, EMG HV, EMGchange, extension deficit for wrist flexors (FCR, FCU), and finger flexors (FPL, FDP, and FDS)) across the three measurements (preoperative, 6 months postoperative, 1 year postoperative) will be examined using one-way repeated measures ANOVA. If histogram analysis and the Kolmogorov-Smirnov test indicate that the data are not normally distributed, the Friedman test will be used as a non-parametric alternative to ANOVA for comparing the three measurements.

The significance level α is set at 0.05. For significant differences, a post hoc paired t-test will be conducted, with α adjusted for multiple testing using the Bonferroni-Holm correction.

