## Discussion

The project aims to develop an instrumented assessment method to differentiate between wrist and finger spasticity. As a secondary goal, a simulation of potential surgical outcomes is planned. If the developed methodology is successfully implemented, patients with upper limb spasticity could be optimally treated with a single surgical intervention that corrects all deformities, within the framework of so-called “single-event-multilevel surgeries.” This approach could spare patients from previous clinical testing through botulinum toxin injections and multiple surgeries with extended hospital stays by providing a clear diagnosis and treatment plan. Additionally, the instrumented outcome measure would serve as a crucial quality control for the surgical therapy.

The long-term goal is to establish a large multicentric database. This will allow for the continued investigation and assessment of individual surgical steps, despite the varying combinations of surgical procedures, and enable an evaluation of their effectiveness over time. It will offer patients a significant improvement in independence and, consequently, quality of life.

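### The pre/post EMG tests are not limited to patients whose analysed muscle was operated on, so unoperated muscles dilute the change and Table 2's power does not carry over

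*Protocol article*

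**What the plan says.** The Statistical analysis section fixes two pre/post comparisons: a paired t-test (or Wilcoxon test) at the interim, once at least 15 patients have a 6-month measurement, and a repeated-measures ANOVA (or Friedman test) at the end. Both use the same outcome list: EMG LV, EMG HV, EMGchange and "extension deficit for wrist flexors (FCR, FCU), and finger flexors (FPL, FDP, and FDS)) across the three measurements". Nothing in that section makes a test depend on whether, or how, the muscle was operated on.

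Surgery is described as mixed. The Introduction says of surgical therapy: "This usually consists of a combination of tendon and nerve procedures". Hypothesis (d) is about measuring improvement "after hyperselective neurectomy, tendon lengthening, and/ or transposition". The patient inclusion criterion is "Patients with spasticity of the upper extremity and an indication for surgery"; it does not require that any particular wrist or finger flexor be operated on.

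The pre/post sample size ("one-sided, α = 0.05, power (1-β) = 0.8) (Table 2") rests on this row: "EMGchange (n = 7) 21.7 23.7 7.4 4.2 0.65 16". Its source is a measurement "in 7 patients with elbow flexor spasticity who underwent hyperselective neurectomy (HSN) of the elbow flexors". In those data every patient had the same procedure on the muscle group that was measured.

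**The concern.** The design effect and the planned analysis describe different quantities. Table 2 gives the change in a muscle group that was operated on. The planned test for, say, FCR gives the average change in FCR over all operated patients, including those whose surgery left FCR alone.

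Hypothesis (d) asks whether the method can measure postoperative improvement. If a muscle-level test shows little change, the plan cannot tell an insensitive method from a muscle that was not treated in many of the patients. The estimated mean change is diluted whatever the sample size.

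Transposed muscles raise a separate question of interpretation. EMGchange is measured during passive wrist or thumb extension, and the same stretch may no longer load a transposed muscle in the same way. Its values before and after surgery may then not measure the same thing.

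**Working it through.** **Inputs from Table 2.** Mean 21.7 before and 7.4 after surgery, so the mean change is 21.7 − 7.4 = 14.3. Effect size dz = 0.65, n = 16, one-sided α = 0.05, power 0.8. The implied SD of the change is 14.3 / 0.65 = 22.0.

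**Reproducing the plan's figure.** For a paired t-test with noncentral t (15 degrees of freedom, noncentrality 0.65 × √16 = 2.6), power at n = 16 is 79.8%. The exact requirement for 80% is 17 and the normal approximation gives 15. The stated 16 is therefore reproduced to within one patient, for a population in which every analysed muscle was treated.

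**Assumed inputs, not in the document.** p is the share of patients in whom the analysed muscle was treated. In untreated muscles the mean change is set to 0, with SD of change s0. I vary s0 from 0.1 to 23.7. Both ends are borrowed from SDs in the sample size tables: the healthy group in Table 1 and the preoperative value in Table 2. Neither is an SD of change in unoperated muscles, so they serve only to bracket the answer.

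**Dilution model.**

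- Mean change = p × 14.3
- Variance of change = p × 22.0² + (1 − p) × s0² + p(1 − p) × 14.3²
- dz = mean change / √variance

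Worked example, p = 0.5 and s0 = 23.7: mean = 7.15; variance = 0.5 × 484 + 0.5 × 561.69 + 0.25 × 204.49 = 242 + 280.8 + 51.1 = 574.0; SD = 23.96; dz = 7.15 / 23.96 = 0.298; one-sided power at n = 16 is 31%.

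| Share treated | s0 | Mean change | dz | Power, n = 16 | n for 80% |
|---|---|---|---|---|---|
| 100% | – | 14.3 | 0.65 | 80% | 17 |
| 75% | 23.7 | 10.7 | 0.46 | 55% | 31 |
| 75% | 11 | 10.7 | 0.52 | 63% | 25 |
| 75% | 0.1 | 10.7 | 0.54 | 66% | 23 |
| 50% | 23.7 | 7.15 | 0.30 | 31% | 71 |
| 50% | 11 | 7.15 | 0.38 | 42% | 45 |
| 50% | 0.1 | 7.15 | 0.42 | 48% | 37 |

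The mixture is not normal, so I also simulated it. The results agree within about 2 percentage points; the largest differences are at s0 = 0.1, where simulation gives about 68% and 50%.

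**Treated-only test in the same 16 patients.** dz stays at 0.65 and n falls to 16p: n = 12 gives 68%, n = 8 gives 51%. To have 16 treated patients for a given muscle, 16 / 0.75 = 22 (rounded up) or 16 / 0.5 = 32 would have to be enrolled.

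**The case against.** The strongest reply is that the article lists muscles; it does not say that treated and untreated muscles are pooled. A condensed article may leave to a fuller plan which patients enter each test, and recording EMG in all specified muscles concerns data collection. This has some force: that every flexor is tested in every patient is an inference. But the article does fix the outcomes, the muscle list, the tests and the sample size, and as stated these do not fit the surgery that it describes. The limitations section discusses mixed aetiology, not mixed surgery.

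Three stronger readings are tempting and should not be drawn.

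- **That restricting to treated muscles brings a large gain in power.** This depends on s0. With s0 = 23.7 the gain is 13 points at 75% treated (68% against 55%) and 20 points at 50% (51% against 31%). But 23.7 is a spread between patients before surgery, not an SD of change. With s0 near zero the gain is 2 to 3 points by formula and 1 point or less by simulation. What remains is the diluted mean.
- **That transposed muscles bias the result toward success.** Hypothesis (d) names transposition only in general terms, with no muscle, route or frequency. The direction of any bias is not established.
- **That the authors acknowledge the problem for this analysis.** The Discussion's phrase "despite the varying combinations of surgical procedures" concerns a future multicentric database, so I do not rely on it.

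Restriction also has a statistical drawback. Muscles selected for surgery may have high preoperative values, so part of their fall may be regression to the mean. Unoperated flexors are an imperfect comparator, because they may differ at baseline and the limitations section itself expects substantial forearm cross-talk.

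**Conclusion.** The concern holds in a limited form. Followed as written, the pre/post EMG tests mix operated and unoperated muscles, and the estimated mean change shrinks in proportion to the share treated: from 14.3 to 10.7 at 75% and to 7.15 at 50%. The 80% power in Table 2 applies only if the analysed muscle was treated in every patient. Otherwise it is about 55-66% at 75% treated and 31-48% at 50% treated. These figures assume the share treated, a zero mean change in unoperated muscles and their SD of change; none of the three is in the document, and spill-over or cross-talk could make the mean change non-zero. The dilution itself needs only that unoperated muscles change less on average than operated ones. The main gain from correction is an estimate that answers hypothesis (d); the gain in power may be small. The point should be settled before the interim analysis.

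**What to change.** 1. Code for each patient and each listed flexor, from the operation report, whether it was operated on and by which procedure.
2. Before the interim analysis, define the primary pre/post EMGchange test for each muscle on the patients in whom that muscle had neurectomy or lengthening. Use the same set for EMG LV and EMG HV.
3. Report unoperated flexors separately, as a descriptive within-patient comparison, with a note on cross-talk and baseline differences.
4. Report transposed muscles separately, stating that the values before and after surgery may not be comparable and that the direction of any bias is unknown.
5. State that the power in Table 2 refers to the number of patients with the analysed muscle treated, and report that number for each muscle.

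A per-patient mean over operated flexors is an option, not a requirement. It keeps more patients, but it merges muscles stretched by different manoeuvres and its make-up differs between patients.

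The cost is the coding work, a smaller n per muscle and possible regression to the mean in muscles selected for surgery, which should be named as a limitation. No visit, measurement or part of clinical care changes.

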### Detailed work plan

The instrumented assessment of wrist and finger spasticity will be analogous to clinical spasticity testing, capturing MAS and TS through slow and fast passive stretching of the muscle groups to be tested. During this process, sEMG signals and relevant joint angles will be measured using 3D motion analysis. Concurrently, subjective MAS and TS values will be recorded.

**Surface EMG and Motion Analysis**: sEMG signals and joint angles will be recorded during slow (30°/s) and fast (180°/s) passive stretching of the muscle groups [20]. A 5-second pause will be maintained between each repetition. The protocol includes the following passive stretches:Wrist extension with a clenched fist (particularly targeting FCU, FCR)Wrist extension with open fingers (targeting FDS, FDP, FCU, FCR)Thumb extension with the wrist in a neutral position (targeting FPL)**Measurement Procedure**: Stretching will be performed manually to ensure clinical applicability. Measurements will be taken with a metronome to maintain speed consistency and include inter-rater reliability testing.**Musculoskeletal Modeling**: A musculoskeletal model generated from 3D motion analysis will be applied to predict postoperative outcomes based on preoperative measurements. Specifically, this involves using preoperative experimental data from the patient and an individually scaled musculoskeletal model, into which the planned surgical procedure (e.g., muscle-tendon lengthening) is incorporated. This allows for the simulation of potential surgical outcomes, such as changes in joint range of motion or the patient’s ability to generate functional movement. For musculoskeletal modeling, the dynamic upper extremity model developed by Saul and Holzbaur [21] was selected due to its high level of anatomical detail, ranging from the thorax to the wrist. The model includes 22 segments and 15 degrees of freedom. Additionally, it represents 32 muscles using 50 Hill-type muscle-tendon actuators. Forward dynamics simulations will be conducted using EMG data as input.**Measurement Time Points** (Fig 1):**HEALTHY PARTICIPANTS:** Two measurements, 7 days apart (***t***_***1***_***, t***_***2***_**)****PATIENT:** Four measurement points, if possible: 8 days preoperative (t_1_), 1 day preoperative (t_2_), 6 months postoperative (t_3_), and 1 year postoperative (t_4_).

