### Statistical analysis

To determine the reliability of the proposed instrumented assessment protocol, a total of 20 patients with spasticity will be included. These patients must not have undergone prior surgery distal to the elbow and must not have received botulinum toxin injections within the past 6 months. A preoperative measurement will be conducted twice for each patient within 1 week to assess the repeatability (test-retest reliability) of the proposed assessment. By correlating the outcome parameters of the two measurement time points, the Intraclass Correlation Coefficient (ICC, interval-scaled data) will be calculated. Similarly, the ICC for healthy participants will be calculated based on the two measurements 1 week apart. The inter-rater reliability will be determined for healthy participants and for patients with spasticity using the measurement at the first time point each. For this purpose, all spasticity assessments will be conducted by two trained examiners. The ICC will then be calculated by correlating the outcome parameters. Standard Error of Measurement (SEM) and Minimal Detectable Difference (MDD) will be reported.

The 20 arms of the healthy participants may include both arms from the same individual. However, measurements will be performed on two separate days. We assume that each arm functions independently without influencing the other side and therefore treat all arms as independent samples, regardless of whether data from both arms of a single participant are included.

A validity analysis in the strict sense is not possible for the proposed methodology, as there is currently no non-invasive valid measurement technique for assessing spasticity. Alternatively, in clinical practice, the subjective scales MAS and TS are used with moderate reliability. Accordingly, the correlation of the determined spasticity parameters by the instrumented assessment method with both scales will be calculated. For this, the Spearman rank correlation coefficient (minimum ordinal data) will be used.

The study design concerning pre-/post treatment analysis corresponds to an experimental prospective cohort study. Initially, the normal distribution of the interval-scaled parameters will be confirmed (Kolmogorov-Smirnov test and visual inspection using histograms).

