### Study limitations

There are some study limitations that have to be addressed and taken into account when interpreting the data. First there is no consensus on how to normalize EMG data in patients with spasticity. MVIC normalization is most commonly performed, although its well-known limitations in patients with reduced voluntary motor control. There exist no SENIAM guidelines for sEMG electrode placement on the forearm. The muscle bellies are very close together and partially overlap, suggesting significant cross-talk. As a result, it is unclear how reliably the sEMG data can be interpreted on the forearm. All electrode and marker placements will be documented with photographs. The recorded sEMG data will be visually inspected and assessed for potential cross-talk. The measurement effort for each individual patient is approximately 1 hour under the study protocol and needs to be minimized for implementation in clinical routine. Due to the low number of eligible patients, the study group will be heterogeneous and include individuals with CP post-stroke, and post-hemorrhagic spasticity. This has to be considered when interpreting data. Concerning the spasticity itself, there are no differences expected between patient groups. When evaluating upper limb function differences in learned and lost (post-stroke, post-hemorrhage) versus never learned (CP) movement patterns to due disturbed volitional motor control must be considered. At least for test-retest reliability in patients the additional effort for a second preoperative measurement might be too high and there might be not enough patients to be included for this special testing. On the other hand, spasticity is highly influenced by daily conditions, environment, emotional state, and temperature – raising the question of whether a test-retest measurement truly assesses the method itself or merely reflects fluctuations in the patient’s condition.

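### The final three-visit repeated measures ANOVA uses only complete patients, relies on a sphericity that Table 2 makes implausible, and leaves the preoperative value undefined

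*Protocol article*

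**What the plan says.** The Statistical analysis section fixes the final test. EMG LV, EMG HV, EMGchange and extension deficit "across the three measurements (preoperative, 6 months postoperative, 1 year postoperative) will be examined using one-way repeated measures ANOVA". If the data do not look normal, "the Friedman test will be used as a non-parametric alternative to ANOVA for comparing the three measurements". A significant result is followed by paired t-tests with Bonferroni-Holm adjustment. Normality is the only assumption that the section checks.

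The visit schedule is conditional. The Detailed work plan lists "Four measurement points, if possible": two before surgery (t1, t2), then 6 months (t3) and 1 year (t4). The Participants section has patients measured "preoperatively (and potentially a second time one week later), 6 months postoperatively, and 1 year postoperatively if surgery is performed". The Statistical analysis section gives the repeat preoperative visit its own purpose: "A preoperative measurement will be conducted twice for each patient within 1 week to assess the repeatability (test-retest reliability) of the proposed assessment". Study limitations adds that "the additional effort for a second preoperative measurement might be too high and there might be not enough patients to be included".

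Table 2, the basis of the pre/post sample size, reads "EMGchange (n = 7) 21.7 23.7 7.4 4.2 0.65 16": means of 21.7 and 7.4, SDs of 23.7 and 4.2, effect size 0.65 and N = 16.

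**The concern.** The test that the protocol names fits its own design and pilot data poorly in three ways.

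- **Incomplete patients.** One-way repeated measures ANOVA and Friedman, as usually run, need all three values from a patient. Someone seen before surgery and at 6 months but not at 1 year adds nothing to the omnibus test, and switching to Friedman does not help.
- **Sphericity.** The ANOVA F-test holds its level only if the three between-visit differences have equal variances. A postoperative SD less than one fifth of the preoperative SD puts this in doubt, and no check or correction is named.
- **Baseline.** The ANOVA has one preoperative level, but a patient may have t1 and t2. No section says whether t1, t2 or their mean is used. That leaves a choice open after the data are seen, on the most variable measurement in the comparison.

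At stake are the level of the omnibus test, usable data in a study of 16 to 20 patients, and a clear definition of change from baseline.

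**Working it through.** **Inputs from the protocol.** Table 2: preoperative 21.7 (SD 23.7), postoperative 7.4 (SD 4.2), effect size 0.65, N = 16, one-sided α 0.05, power 0.80. Not given, so assumed with a range: the 1-year SD, the correlations involving the 1-year visit, the share of incomplete patients and the test-retest ICC.

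**The plan's own figure.** For a paired one-sided test with effect size 0.65, the normal approximation ((1.645 + 0.842)/0.65)² = 14.6 gives 15 patients. The exact noncentral t gives 17, with power 0.798 at 16. The stated 16 is therefore reproduced closely, and it contains no allowance for loss.

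**Incomplete patients.** Assumed shares without all three visits, with the paired one-sided power of the complete patients:

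| Incomplete (assumed) | Complete of 16 | Power | Enrolled to keep 16 |
|---|---|---|---|
| 10% | 14 | 0.74 | 18 |
| 20% | 12 | 0.68 | 20 |
| 30% | 11 | 0.64 | 23 |

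**Sphericity.**
1. SD of the pre/post difference: (21.7 − 7.4)/0.65 = 14.3/0.65 = 22.0, so the variance is 484.
2. Implied pre/post correlation: (23.7² + 4.2² − 22.0²)/(2 × 23.7 × 4.2) = 0.48.
3. Whatever that correlation, Var(pre − post) lies between (23.7 − 4.2)² = 380 and (23.7 + 4.2)² = 778. If both postoperative visits have SD 4.2, Var(6 months − 1 year) cannot exceed (4.2 + 4.2)² = 71. In that case the variances cannot be equal.
4. With a 1-year SD of 4.2 and a 6-month to 1-year correlation of 0 to 0.8, the three variances are 484, 484 and 7 to 35. The Greenhouse-Geisser epsilon is 0.51 to 0.56, where 0.50 is the minimum.
5. Simulated rejection of the uncorrected F-test at n = 16 under normal data and equal means, with all correlations near 0.48:

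| Assumed 1-year SD | Epsilon | Rejection at nominal 5% |
|---|---|---|
| 4.2 | 0.53 | about 8.4% |
| 8.4 | 0.59 | about 7.8% |
| 12 | 0.69 | about 7.0% |
| 16 | 0.83 | about 5.9% |
| 23.7 | 0.98 | about 5% |

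6. Greenhouse-Geisser brings the first row back to about 5%. Its price, with means 21.7/7.4/7.4 and a 1-year SD of 4.2, is omnibus power of about 0.69 instead of 0.78.
7. The full planned sequence (ANOVA, then Holm-adjusted paired t-tests) declares any pairwise difference in only 2 to 3% of samples with equal means.

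**Baseline.** Averaging t1 and t2 removes half of the baseline error variance, (1 − ICC) × 23.7²/2, from 484. At ICC 0.7 this is 0.3 × 561.7/2 = 84.3, and 84.3/484 = 17%.

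| Assumed ICC | Variance cut | Effect size (from 0.65) |
|---|---|---|
| 0.5 | 29% | 0.77 |
| 0.7 | 17% | 0.72 |
| 0.8 | 12% | 0.69 |
| 0.9 | 6% | 0.67 |

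These gains apply to patients who have both preoperative visits.

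**The case against.** Repeated measures ANOVA with Friedman as fallback and Holm post hoc tests is a conventional choice, and a journal article may leave a sphericity correction and the handling of missing visits to an analysis plan that is not shown. This has weight: the text states no complete-case rule, and silence on missing data is not itself a fault. But the article does fix the tests, and those tests have these properties.

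Four stronger readings are tempting, and the documents do not support them.

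- **That Table 2 contradicts sphericity.** It has two occasions, 7 patients, elbow flexors and EMGchange only. Sphericity concerns three visits. If the 1-year SD came back near 23.7, the F-test would be about right. Data this skewed may also lead to Friedman, which does not assume sphericity.
- **That false claims about specific visits are inflated.** They are not. The paired tests do not need sphericity.
- **That patients lost at 1 year vanish from every 6-month result.** The interim paired test of preoperative against 6-month values, in at least 15 patients, does not need the 1-year visit.
- **That the second preoperative visit is wasted.** It serves test-retest reliability, and it is optional. Using one preoperative value is not an error in itself. Leaving open which one is a gap.

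On loss of patients, the 20 planned for the reliability part could give some margin if all have surgery and follow-up, but the protocol does not say so. The one visit shortfall it discusses explicitly is that of the second preoperative measurement, which the three-level ANOVA does not need.

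**Conclusion.** The point holds as a cheap improvement, not as a flaw that invalidates the study. The named tests cannot use a patient with a missing visit, while the schedule is conditional and N = 16 has no margin. The omnibus F-test would reject in roughly 7 to 8.4% of null samples if the 1-year SD lies between 4.2 and 12, and close to 5% if it returns near the preoperative 23.7. A lasting reduction in spasticity would suggest the lower SDs, but the protocol has no 1-year data to settle this. The inflation is confined to the omnibus p-value. The baseline value is undefined. The rejection rates rest on normal data, n = 16, the Table 2 SDs carrying over from elbow to wrist and fingers, and correlations near 0.48. The loss rates and ICCs are assumptions.

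**What to change.** 1. Analyse EMGchange and the other outcomes with a linear mixed model that uses every available visit and allows visit-specific variances. Report the baseline-to-6-month and baseline-to-1-year contrasts with confidence intervals.
2. If repeated measures ANOVA is kept, apply the Greenhouse-Geisser correction and state how patients with a missing visit are handled.
3. Fix the baseline before the final analysis: the mean of t1 and t2 where both exist, otherwise the single preoperative value.

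The cost is analysis wording and code, with no extra measurements or patients. With 16 to 20 patients the mixed model may not converge, so a simpler covariance should be named in advance as fallback. The Greenhouse-Geisser route gives up some omnibus power, as shown above. A baseline that is a mean for some patients and a single value for others differs in precision between patients, which should be stated when the results are reported.
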